**Exploratory outcome measures**	
◦ *Proportion of participants in the intervention arm successfully delabelled post oral challenge* ◦ *Proportion of participants in the intervention arm with positive repeat oral challenge (post-ICU discharge)* ◦ *Utilisation of any penicillin during hospital admission* ◦ *Utilisation of any narrow-spectrum beta-lactam during hospital admission* ◦ *Utilisation of vancomycin during hospital admission* ◦ *Utilisation of any restricted antibiotic during hospital admission* ◦ *In-Hhspital and 30-day mortality* ◦ *ICU length of stay and hospital length of stay*	

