## Methods/design

### Study objectives

To investigate the feasibility and safety of a direct oral penicillin challenge in adult ICU patients that have a low-risk penicillin allergy (PEN-FAST score < 3). Outcome measures are listed in Table 1 and include the primary outcomes of safety and feasibility of direct oral challenge. Secondary outcomes include proportion of allergy labels removed post-oral challenge, proportion of positive repeat oral challenges, pre- and post-randomisation antimicrobial utilisation, in-hospital and 30-day mortality and length of stay.

**Table 1 Tab1:** Outcome measures

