### Intervention and control arms

#### Intervention

The intervention is a single dose 250 mg of oral penicillin (capsule or liquid via enteral route, including nasogastric/PEG/PEJ) following baseline observations being performed (i.e. temperature, heart rate, blood pressure, respiratory rate, skin check). The implicated penicillin will be administered if known. Amoxicillin will be administered for “penicillin unspecified” allergy labels (or penicillin VK if the reaction occurred prior to the availability of amoxicillin). The penicillin challenge dose will be charted by the study or ICU clinician (following review of baseline observations) and administered by bedside nursing staff. Clinical observations will be collected by the bedside nursing staff at + 30, + 60, + 90 and + 120 min post-oral challenge. If at any stage an antibiotic-associated adverse event is noted, the treating and study clinicians will be informed. Treatment of the adverse event will be at the discretion of the treating clinician.

Patients will undergo a repeat single-dose oral penicillin (250 mg) challenge (if initial challenge is negative) following ICU discharge and at least 48 h post-initial challenge (if they remain an inpatient). Participants who no longer require ICU-level care but have not yet been transferred out of the unit due to bed availability may receive the repeat oral challenge within the ICU if at least 48 h have passed since the primary challenge dose. A further set of clinical observations at 30-min intervals over 2 h will be collected following the repeat oral challenge. The repeat challenge is administered to assess for a potential false-negative initial oral challenge secondary to critical illness. Participants will be reviewed at 24 h and 5 days post-randomisation; 24 h and 5 days post the second oral challenge and 90 days post-randomisation. Participant review will assess for any serious or antibiotic-associated adverse events as per protocol definitions and will be undertaken in-person whilst an inpatient or via telephone or telehealth following hospital discharge. Participants with a positive initial challenge will not proceed to a repeat challenge.

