### Statistical methods

Data analysis will be performed on an intention-to-treat basis as well as per protocol. Summary statistics will be used to describe the clinical data and presented as mean ± standard deviation (SD), median with interquartile range (IQR) or percentages as appropriate.

Feasibility and safety outcomes will be reported as percentage with 95% confidence intervals. Logistic regression will be used to compare antibiotic utilisation and mortality between groups. Results will be reported as odds ratios with 95% confidence intervals. Negative binomial regression will be used for comparison of length of stay (reported as incidence rate ratio with 95% CI). Results will be reported according to CONSORT guidelines [17].

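### The any-penicillin utilisation outcome counts the trial's own challenge doses, and its time window differs between Table 1 and the objectives

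*Protocol article*

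**What the plan says.** All references are to the protocol article.

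- **Table 1, exploratory outcome measures**, has four antibiotic outcomes, each counted over the whole admission: "Utilisation of any penicillin during hospital admission", "Utilisation of any narrow-spectrum beta-lactam during hospital admission", "Utilisation of vancomycin during hospital admission" and "Utilisation of any restricted antibiotic during hospital admission". No start at randomisation is given, and no dose is excluded.
- **Intervention:** "The intervention is a single dose 250 mg of oral penicillin". A second 250 mg dose follows a negative first challenge, after ICU discharge (or in the ICU if only a bed is awaited) and at least 48 h later, for patients still in hospital.
- **Control:** routine management with matched observations and no challenge dose.
- **Study objectives** describe the same outcome family as "pre- and post-randomisation antimicrobial utilisation".
- **Statistical methods:** "Logistic regression will be used to compare antibiotic utilisation and mortality between groups", reported as odds ratios with 95% confidence intervals. Analyses are by intention to treat and per protocol. The window to be modelled is not stated.

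**The concern.** An outcome meant to show whether the challenge changes later prescribing should not be satisfied by the challenge itself. Under the Table 1 wording, a patient in the intervention arm becomes a penicillin user on taking the allocated dose. The outcome then largely repeats the feasibility measure of whether the intervention was delivered, and the between-arm odds ratio reflects allocation instead of prescribing.

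The second problem is the window. Antibiotics given before randomisation cannot be affected by allocation. Table 1 would count them together with later use, whereas the objectives appear to separate the two periods.

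At stake is how far the prescribing estimates can be used. The Sample size section says the pilot will supply local estimates for later power calculations, and the abstract and Discussion say that the follow-on trials will examine antimicrobial prescribing. A penicillin estimate produced by the study dose would mislead that planning.

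**Working it through.** **The plan's own figure.** The Sample size section assumes 200 eligible patients, 50% recruitment and 85% completion: 200 × 0.50 × 0.85 = 85, as stated. The target is then set at 80, or 40 per arm. No effect size or power is given for the utilisation outcomes.

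**Step 1: all 40 challenged.** Intervention-arm use is 40/40. If controls include both users and non-users, the intervention arm has an empty non-user cell. This is quasi-complete separation, and the maximum-likelihood odds ratio is not finite. A per-protocol set restricted to challenged patients has the same empty cell by definition.

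**Step 2: 34 of 40 challenged.** This borrows the 85% completion figure as an assumed delivery rate: 0.85 × 40 = 34, so the floor is 34/40 = 85%. Suppose there is no prescribing effect, so that the 6 unchallenged patients use penicillin at the control rate. Control use is assumed. Its two upper values are the Background rates of narrow-spectrum beta-lactam use (39.5% and 58.8%), used here only as plausible levels. Counts are rounded to whole patients.

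| Assumed control use | Control users | Intervention users | Odds ratio |
|---|---|---|---|
| 10% | 4/40 | 34 + 1 = 35/40 | (35 × 36)/(5 × 4) = 63 |
| 20% | 8/40 | 34 + 1 = 35/40 | (35 × 32)/(5 × 8) = 28 |
| 39.5% | 16/40 | 34 + 2 = 36/40 | (36 × 24)/(4 × 16) = 13.5 |
| 58.8% | 24/40 | 34 + 4 = 38/40 | (38 × 16)/(2 × 24) = 12.7 |

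The Fisher exact p-value is at most 0.0003 in every row, although prescribing is identical in the two arms. With study doses excluded, the expected odds ratio in every row is 1.

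**Step 3: does a split at randomisation cure this?** No. Both study doses are given after randomisation, so the exclusion has to be stated in its own right.

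**Step 4: pooling earlier use.** Let q be the share already exposed before randomisation, taken as equal in both arms and independent of later use. Then use over the admission is q + (1 − q)p, and the risk difference shrinks by the factor (1 − q). The article gives no value for q. As an illustration only, take post-randomisation use of 39.5% versus 58.8%:

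| Assumed q | Whole-admission use | Difference (points) | Odds ratio |
|---|---|---|---|
| 0 | 39.5% v 58.8% | 19.3 | 2.19 |
| 10% | 45.6% v 62.9% | 17.4 | 2.03 |
| 20% | 51.6% v 67.0% | 15.4 | 1.91 |
| 30% | 57.7% v 71.2% | 13.5 | 1.81 |
| 50% | 69.8% v 79.4% | 9.7 | 1.67 |

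The direction is certain under these assumptions. The size depends entirely on q.

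**The case against.** The strongest reply is that Table 1 holds one-line labels in a condensed article. The Discussion describes the interest as the effect of the challenge on prescribing, so a sensible analyst would not count the study dose, and a full protocol or analysis plan may already say so. This reply bears on how serious the point is, but does not remove it. Table 1 names both the qualifying drug (any penicillin) and the window (the admission), the intervention falls inside both, and the window differs from the one in the objectives. The published definition would need correcting even if an unseen document handles it.

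Several stronger readings are tempting, and the article does not support them:

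- **That earlier prescribing will be pooled, or will bias the comparison.** The objectives name both periods, so a split is foreseen. Randomisation balances earlier use in expectation, so pooling would attenuate the contrast without favouring an arm.
- **That every challenged patient also meets the narrow-spectrum beta-lactam outcome.** This holds only if the challenge agent belongs to that class, which the article does not define by agent.
- **That 85% is the planned delivery rate.** In the Sample size section it is completion of the challenge or observation across both arms, and it is used there to project the pool.
- **That these are the trial's only efficacy data, or the named input to the next power calculation.** Delabelling, mortality and length of stay are also listed, and the Sample size section does not say which estimates will be carried forward.

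**Conclusion.** The point holds for the any-penicillin outcome. As written, that outcome includes the intervention. The planned odds ratio is not finite if all 40 are challenged, and is about 13 to 63 under no prescribing effect if 34 of 40 are. That range rests on assumed delivery of 85% and assumed control use of 59% down to 10%. The narrow-spectrum outcome is affected only conditionally, depending on how the class is defined.

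The mismatch between the whole-admission window and the split in the objectives is a real inconsistency. Its cost is lost contrast, of a size that cannot be computed from the article.

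This should be fixed, but it does not threaten the trial's main conclusions. Table 1 labels these outcomes exploratory (the objectives call them secondary), and the feasibility threshold of at least 50% recruitment and the safety threshold below 5% do not depend on them. The harm would fall on the prescribing estimates and on any planning that relies on them.

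**What to change.** State that study challenge doses, both first and repeat, are excluded from all antibiotic-utilisation outcomes. Compare the arms on use from randomisation onward, with randomisation as the single time zero. Report use before randomisation separately, or enter it as a covariate where it is recorded. Align the study objectives, Table 1 and the statistical methods on this definition, and list the agents that count as narrow-spectrum beta-lactams.

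The cost is a sentence or two of text and a filter at analysis. The Data collection section covers antimicrobial treatment and challenge data. It does not say whether dose dates are captured, so this should be checked against the full data list in Additional file 3. No change to recruitment, the intervention or the primary outcomes is needed.

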### Design and schedule

This is a pilot, feasibility, open-label randomised clinical trial that will be conducted in mixed medical/surgical ICUs in five tertiary referral teaching hospitals in Melbourne, Australia (Austin Health, Peter MacCallum Cancer Centre, Melbourne Health, Monash Health, Alfred Health). A summary of the study design is presented in Fig. 1. We will include 80 patients with a low-risk penicillin allergy and allocate them in a 1:1 ratio to the intervention group (oral penicillin challenge) and control group (standard of care). Oral challenge will be undertaken using the implicated oral penicillin if known (including penicillin VK, amoxicillin, flucloxacillin, dicloxacillin). Challenge for “penicillin unspecified” allergy labels will utilise amoxicillin (the most common community-prescribed oral penicillin in Australia) [15] or penicillin VK (if the reaction occurred prior to amoxicillin availability).

**Fig. 1 Fig1:**
[figure not shown]
Summary of ORACLE study design

Adult patients admitted to the ICU reporting a penicillin allergy will be identified by study investigators from a daily electronic medical record (EMR) list and assessed utilising a validated Antibiotic Allergy Assessment Tool (Additional file 1) to obtain allergy phenotype [16]. Once the reported allergy phenotype has been determined, the PEN-FAST clinical decision rule will be applied (Additional file 2). Informed consent will be sought from those with a PEN-FAST score < 3 who meet all eligibility criteria, and they will be randomised to the intervention arm or control arm. All other concomitant care and interventions will be undertaken according to local ICU and hospital protocols.

### Eligibility criteria

#### Inclusion criteria

Inclusion criteria will include adult (≥ 18 years) ICU inpatients reporting a penicillin allergy with a PEN-FAST assessment score of less than 3 (representing a low or very low risk of true penicillin allergy) and an expected ICU discharge date of > 24 h post-randomisation.

#### Exclusion criteria

Patients will be excluded if their allergy history cannot be confirmed, they are severely critically ill (unlikely to survive index admission, high ventilatory support requirements, high inotropic support requirements), with confirmed pregnancy, they are receiving medication that may interfere with allergy assessment (antihistamines, high-dose steroids), or they report a history of non-penicillin drug-associated anaphylaxis or idiopathic urticaria/anaphylaxis/mastocytosis.

A full list of inclusion and exclusion criteria is presented in Table 2.

**Table 2 Tab2:** ORACLE study eligibility criteria

**Inclusion criteria**
1. Adult (≥ 18 years) ICU inpatient
2. Reported penicillin allergy with a PEN-FAST score < 3
3. Are expected to stay in the ICU at least 24 h post-assessment
**Exclusion criteria** (patient excluded if **ONE** of the following criteria present)
1. Known pregnancy
2. Death is deemed imminent or inevitable during this admission, and either the attending physician, patient or medical treatment decision-maker is not committed to active treatment
3. Any other illness that, in the investigator’s judgement, will substantially increase the risk associated with subject’s participation in this study
4. Patients with known history of ANY non-penicillin drug-associated anaphylaxis
5. Patients with a known history of idiopathic urticaria, idiopathic anaphylaxis or mastocytosis
6. Patients where the allergy history was not able to be confirmed with patient or medical treatment decision-maker
7. Patients on antihistamine therapy (excluding H2-receptor antagonists)
8. Patients receiving > 10 µg/minute of noradrenaline or any adrenaline therapy in the last 4 h
9. High ventilator requirement if intubated (any of the following) i. Any mode other than spontaneous ii. Peak end-expiratory pressure (PEEP) > 5 cm H2O iii. FiO2 > 40%
10. Patients receiving more than stress dose steroid therapy (i.e. > 50 mg QID hydrocortisone or daily equivalent)

### Intervention and control arms

#### Intervention

The intervention is a single dose 250 mg of oral penicillin (capsule or liquid via enteral route, including nasogastric/PEG/PEJ) following baseline observations being performed (i.e. temperature, heart rate, blood pressure, respiratory rate, skin check). The implicated penicillin will be administered if known. Amoxicillin will be administered for “penicillin unspecified” allergy labels (or penicillin VK if the reaction occurred prior to the availability of amoxicillin). The penicillin challenge dose will be charted by the study or ICU clinician (following review of baseline observations) and administered by bedside nursing staff. Clinical observations will be collected by the bedside nursing staff at + 30, + 60, + 90 and + 120 min post-oral challenge. If at any stage an antibiotic-associated adverse event is noted, the treating and study clinicians will be informed. Treatment of the adverse event will be at the discretion of the treating clinician.

Patients will undergo a repeat single-dose oral penicillin (250 mg) challenge (if initial challenge is negative) following ICU discharge and at least 48 h post-initial challenge (if they remain an inpatient). Participants who no longer require ICU-level care but have not yet been transferred out of the unit due to bed availability may receive the repeat oral challenge within the ICU if at least 48 h have passed since the primary challenge dose. A further set of clinical observations at 30-min intervals over 2 h will be collected following the repeat oral challenge. The repeat challenge is administered to assess for a potential false-negative initial oral challenge secondary to critical illness. Participants will be reviewed at 24 h and 5 days post-randomisation; 24 h and 5 days post the second oral challenge and 90 days post-randomisation. Participant review will assess for any serious or antibiotic-associated adverse events as per protocol definitions and will be undertaken in-person whilst an inpatient or via telephone or telehealth following hospital discharge. Participants with a positive initial challenge will not proceed to a repeat challenge.

#### Control

Routine management of penicillin allergy label as per local ICU protocols without oral penicillin challenge. Patients in the control arm will have observations performed at randomisation and at + 30, + 60, + 90 and + 120 min post-randomisation by the bedside nursing staff. A further set of clinical observations at 30-min intervals over 2 h will be collected following ICU discharge and at least 48 h after randomisation (if they remain an inpatient). Participants will be reviewed at 24 h and 5 days post-randomisation, 24 h and 5 days post the second observation period and 90 days post-randomisation. Participant review will assess for any serious or antibiotic-associated adverse events as per protocol definitions and will be undertaken in-person whilst an inpatient or via telephone or telehealth following hospital discharge. After the completion of the 90-day review, all participants in the control arm will be offered a referral to their nearest public antibiotic allergy assessment clinic for definitive assessment of their penicillin allergy label.

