**Primary outcome measures**	
* Feasibility outcome measures*	
* Eligibility to screened ratio*	Proportion of patients that are eligible for intervention
*** Recruitment to eligibility ratio***	Proportion of eligible patients consenting to the participation in the study *(a ratio of* ≥ *50% will be used as the primary determinant of feasibility)*
* Intervention to recruitment ratio*	Proportion of patients randomised to the intervention arm that had the intervention delivered as per protocol
* Protocol compliance*	Proportion of randomised patients that complete all study activities as per protocol
* Safety outcome measures*	
* Safety*	Proportion of patients with a penicillin allergy who experience an antibiotic-associated immune-mediated adverse event OR serious adverse event *(a proportion of* < *5% will be used as the determinant of safety)*

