#### Harms

Serious adverse events (SAEs) will be defined as any adverse drug event that, in the opinion of the investigators, is causal for any of these outcomes: (1) death; (2) life-threatening reaction; (3) inpatient hospitalisation; (4) results in persistent or significant disability/incapacity; (5) congenital anomaly or birth defect; or (6) requires intervention to prevent permanent impairment or damage. SAEs that occur from the time of commencement of study treatment to 5 days after the second challenge/observation will be collected and reported to the approving ethics committee within 24 h of study staff becoming aware of the event.

An antibiotic-associated immune-mediated adverse event will include any immune-mediated reaction within 48 h of an antibiotic dose judged by two independent reviewers. An antibiotic-associated adverse event will be defined as any non-immune mediated reaction (e.g. diarrhoea, nausea and vomiting) within 48 h of an antibiotic dose judged by two independent reviewers.

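### Only intervention patients waiting for a ward bed may have the second contact in the ICU, so the serious adverse event window can run longer in bed-blocked controls

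*Protocol article*

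**What the plan says.** All references are to the Protocol article.

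- **Intervention.** The repeat challenge normally takes place after ICU discharge and at least 48 h after the first. There is one exception. Participants ready to leave the ICU but held there for want of a bed "may receive the repeat oral challenge within the ICU if at least 48 h have passed since the primary challenge dose".
- **Control.** The parallel observations "will be collected following ICU discharge and at least 48 h after randomisation". No exception for bed delay is given.
- **Harms.** The collection window is tied to this second contact: "SAEs that occur from the time of commencement of study treatment to 5 days after the second challenge/observation will be collected".
- **Table 1, safety outcome.** The primary safety measure is the proportion of patients "who experience an antibiotic-associated immune-mediated adverse event OR serious adverse event", judged against a 5% limit.
- **Statistical methods.** "Feasibility and safety outcomes will be reported as percentage with 95% confidence intervals". No test of safety between arms is described.

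**The concern.** The second contact does two jobs. It is the repeat challenge, or the matching observation period in controls, and it also sets the end of SAE collection. The sponsor foresaw that bed shortage would hold some patients in the ICU and wrote a rule for it, but only for one arm. Two patients with the same clinical course and the same bed delay can then be followed for SAEs for different lengths of time, solely because of allocation.

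At stake is the comparability of the two SAE percentages. The control arm has the same observation and review schedule so that events under routine care can be set beside events after challenge. If controls are observed for longer, they have more time to record an event, and a reader comparing the percentages would see a difference tilted slightly in favour of the challenge.

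**Working it through.** The article states no figure for the window length or for bed delay, so there is no figure to reproduce. The check derives the window from the stated rules.

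**Inputs**
- Earliest second contact: 48 h = day 2 (Intervention; Control).
- SAE collection ends 5 days after the second contact (Harms).
- *r* = day on which ICU-level care is no longer needed (assumed).
- *d* = days then spent waiting for a ward bed (assumed).
- The first challenge is taken to be given at randomisation, so that both clocks start together. The second contact is taken to occur as soon as the rules allow.

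**Formulas**
- Intervention, allowance used: window ends at max(2, *r*) + 5.
- Control: window ends at max(2, *r* + *d*) + 5.
- Difference = max(2, *r* + *d*) − max(2, *r*). For *r* of 2 days or more this equals *d*. For *r* below 2 it is only the part of the delay that falls after 48 h.

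**Results**

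| Ready for ward (*r*) | Bed delay (*d*) | Intervention ends | Control ends | Control longer by |
|---|---|---|---|---|
| day 2 | 0 | day 7 | day 7 | 0 |
| day 2 | 0.5 | day 7 | day 7.5 | 0.5/7 = 7% |
| day 2 | 1 | day 7 | day 8 | 1/7 = 14% |
| day 2 | 3 | day 7 | day 10 | 3/7 = 43% |
| day 4 | 1 | day 9 | day 10 | 1/9 = 11% |
| day 4 | 3 | day 9 | day 12 | 3/9 = 33% |
| day 10 | 0.5 | day 15 | day 15.5 | 0.5/15 = 3% |
| day 10 | 3 | day 15 | day 18 | 3/15 = 20% |

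For a patient ready before 48 h, say *r* = 1 and *d* = 3, the intervention window ends at 2 + 5 = day 7 and the control window at 4 + 5 = day 9. The gap is 2 days, not 3.

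**With the same allowance in both arms**, both windows end at max(2, *r*) + 5 and the difference is 0 for every *d*.

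These are differences in calendar time. The article gives neither the frequency of bed delay nor an SAE rate, so they cannot be turned into expected events.

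**The case against.** There is a fair case that this has little or no consequence.

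- *SAEs are narrowly defined.* Harms limits them to adverse drug events that the investigators judge causal, so extra days waiting for a bed do not add general ICU morbidity. This stands and is the main reason the effect is small.
- *No challenge goes unobserved.* Every repeat dose keeps its 24 h and 5-day reviews, and the immune-mediated component is tied to 48 h after an antibiotic dose, not to this window. This stands. A reader might infer that the shorter intervention window hides reactions to the challenge; the document does not support that.
- *No between-arm safety test is stated.* Correct. A reader might infer that a planned comparison is biased, but none is described. If the 5% limit is applied to the intervention arm alone, the control window does not enter it at all.
- *Both arms are reviewed at 90 days.* This softens the difference. It does not remove it, because that review applies the protocol's definitions and Harms still closes SAE collection 5 days after the second contact. The Harms sentence also covers rapid reporting to the ethics committee and might be meant to govern only that, but it speaks of collection as well.
- *The window already varies between patients, and the allowance is optional.* True, but variation through ICU discharge arises under the same rule in both arms. The bed-delay part is the one that depends on allocation, and it appears only when the allowance is used.
- *The article may have shortened the control text.* Possible, since the full protocol is not shown. But the article states both rules, and as stated they differ.

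A stronger reading also suggests itself from Table 1, which adds in brackets that the repeat challenge is after ICU discharge. A reader might infer that a positive repeat given in the ICU would not be counted. The document does not support this: Study objectives names positive repeat challenges without any limit on location, and the Intervention section expressly permits the in-ICU repeat. The bracket reads as the usual timing. Aligning the wording would be tidy, but it is not a finding.

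**Conclusion.** The point holds as a small, avoidable asymmetry. Read together, the Intervention, Control and Harms sections make the collection window for one component of the primary safety outcome depend on arm for bed-blocked patients. Whenever the allowance is used, a comparable control is followed for longer by the full bed delay if ready for the ward at or after 48 h, and by less if ready sooner.

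The size in days rests on assumed delays. At 0.5 to 3 days the control window is 7% to 43% longer for a patient ready at 48 h, and 3% to 20% longer for one ready at day 10. The 43% is a corner case, since it needs readiness at exactly 48 h followed by a 3-day wait. Only bed-blocked patients in a pilot of 80 are affected, and nothing in the document shows that a reported result or the safety decision would change. It is worth correcting because the correction is so cheap, not because the effect is likely to be large.

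**What to change.** In the Control section, add one sentence: the second observation period may take place in the ICU once ICU-level care is no longer required, provided at least 48 h have passed since randomisation. The arms then follow the same rule and the difference in SAE windows is zero at any bed delay. The cost is that one sentence, with no added procedure or visit.
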